#### Sleep and daily activities instrumental assessments

Actigraphy is a non-invasive method of monitoring cycles of rest and activity; a sensor unit can be worn to measure gross motor activity. The actigraphic sensor unit is similar to a watch and continually records movement.

### Analysis

The general linear model will be used to test interaction effects between treatments (experimental versus control groups) and over time (three repeated measures). Six models will be built, one of each primary outcome measure (quality of life, anxiety, and depression) and separately for patients and caregivers. Type I error inflation due to multiplicity of tests will be controlled by the correction of critical alpha (0.05/6 = 0.008). Violations of the parametric model assumptions will be tested and explored with ad-hoc techniques. If violations are detected, robust methods, data manipulation, or statistical corrections will be applied accordingly. An intention-to-treat analysis approach will be used. Missing data will be imputed with multiple imputation techniques [28]. According to power analysis calculation (G*Power), a total sample size of 110 patients (and caregivers) will allow the detection of small interaction effects (*η*^2^ = 0.01) with a 0.85 statistical power, alpha = 0.05 and an assumed nonsphericity correction (*ε*) of 0.75. Significant interaction effects will be followed by contrast analysis. A similar analysis will be conducted for the actigraphic data, with a reduced sample size, enabling the detection of a small-medium interaction effect under the same conditions.

The mediation effect of the meditation level will be examined by adding a within-subjects factor to the general linear models and the interactions with the treatment effect will be explored according to the guidelines of Kraemer *et al.* [29]. In addition, moderation effects by sex, age, and number of accesses to the software will be examined by adding the relative between-subjects factors into the general linear models and the interactions with the treatment effect will be explored according to the same guidelines [29].

Data analysis will be performed with R and SPSS software.

Data collection and analysis will begin at month 1, and will last 21 months, 1 month after the last follow-up data gathered.

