## Methods/design

### Study design

The study design of the randomized controlled trial is composed of two arms (experimental and control groups, both of 8 weeks duration) and three assessments (2 × 3 design): baseline, directly after treatment, and 6-months follow-up. Each participant will provide informed consent. Ethical committees from both the Catholic University of Milan (reference 19-12-2013) and the Fondazione Don Gnocchi (reference FDG_9.4.14) have approved the project. Results will be published in both scientific and general-audience media.

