### Screening, assessments, and randomization

Screening will be conducted by doctors of the Multiple Sclerosis Center of the Fondazione Don Gnocchi Hospital, considering the inclusion and exclusion criteria.

Subsequently all subjects will be fully assessed at baseline (T1), after 2 months (T2, corresponding to the end of treatment) and at 6-months follow-up (T3).

Primary outcome measures will assess quality of life, together with depression and anxiety. Attained mindfulness level, quality of sleep, and participation level will be considered secondary outcome measures. Questionnaires will be self-reported, with online assessments (therefore accessible from subjects’ own computers). Subjects will be also assessed, with a qualitative approach (semi-structured interview), about possible side effects or adverse events of the treatment, at T2 and T3, by a psychologist. The interview will be conducted in person or via teleconference call (e.g., Skype).

Subsequently, randomization will be conducted by the principal investigator who will be fully blinded to all patient information, except the study identification numbers of patients. Patient–caregiver couples will be considered as single units for the randomization.

Subjects, consisting of patient–caregiver couples, will be randomly allocated into two groups (60 patients + their caregivers for each groups, with a stratification referred to subjects recruited for the instrumental assessment):Meditation telemedicine intervention, developed and tested.Control group, receiving psycho-education, utilizing a telemedicine approach.

The intervention phase will begin at the end of the pilot study (month 6) and will last 11 months.

In the mainframe of the general study, an objective evaluation of the impact of treatment on sleep disturbance and fatigue will be conducted with an instrumental assessment. During the software development and testing phases, we will consecutively recruit 40 subjects with MS (first recruitment round), with the same inclusion criteria, who report disturbed sleep. Each of these subjects will undergo actigraphy. The sensor will be worn by each subject for two consecutive weeks and will provide objective information about quality of sleep and daily activity, with synthetic data summarized by a computer software.

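### The primary test uses the pre-randomisation baseline as an outcome level; it is valid, but adjusting for baseline and testing T2 and T3 jointly is usually more efficient

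*Protocol article*

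**What the plan says.** The Analysis section of the protocol article sets one model for each of three primary outcomes (quality of life, anxiety, depression), separately for patients and caregivers. Each of the six tests uses alpha 0.05/6. The test is stated as: "The general linear model will be used to test interaction effects between treatments (experimental versus control groups) and over time (three repeated measures".

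The Study design section names the occasions: "three assessments (2 × 3 design): baseline, directly after treatment, and 6-months follow-up". Baseline is therefore one of the outcome levels. The section on screening, assessments and randomisation describes the assessments and then continues: "Subsequently, randomization will be conducted by the principal investigator". Nowhere is the baseline score used as a covariate.

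Direction and timing are left to a second step: "Significant interaction effects will be followed by contrast analysis". The power statement is built on the same interaction: "a total sample size of 110 patients (and caregivers) will allow the detection of small interaction effects", with eta-squared 0.01, power 0.85, and "alpha = 0.05 and an assumed nonsphericity correction (*ε*) of 0.75".

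**The concern.** Treatment cannot affect a score taken before allocation, and randomisation gives both arms the same expected baseline. Treating that score as an outcome does not use this knowledge. The interaction hypothesis over T1, T2 and T3 is the joint hypothesis that the arms do not differ in change from T1 to T2 or from T1 to T3. A change score carries the full noise of the baseline measurement, whereas a covariate removes only the part that predicts the later score.

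The cost is precision. It matters more here because each primary test is made at 0.05/6, where power is harder to obtain, and because the data needed for the better analysis are already collected.

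**Working it through.** **Inputs.** From the Analysis section: N = 110 (n = 55 per arm), three occasions, eta-squared 0.01, alpha 0.05 for power and 0.05/6 = 0.0083 for testing, epsilon 0.75. Assumed, because the article does not give them: the correlation rho between occasions, the effect in SD units, and its course over time.

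**The plan's own figure.** For the within-between interaction, lambda = f² × N × m × epsilon/(1 − rho), with f² = 0.01/0.99 = 0.0101, m = 3, and degrees of freedom 2 × 0.75 = 1.5 and 108 × 2 × 0.75 = 162. At rho 0.75, lambda = 0.0101 × 110 × 3 × 0.75/0.25 = 10.0.

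| rho | 0.3 | 0.5 | 0.6 | 0.7 | 0.75 | 0.8 |
|---|---|---|---|---|---|---|
| power at alpha 0.05 | 0.41 | 0.54 | 0.64 | 0.77 | 0.84 | 0.91 |

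The stated 0.85 is met at rho of about 0.755. Because rho is not given, the figure can be neither confirmed nor refuted. At rho 0.75 and alpha 0.0083 the same formula gives 0.62.

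**Variance at one visit (unit variances, equal correlations).** Change from baseline: 2(1 − rho). Adjusted for baseline: 1 − rho². The ratio of adjusted to change is (1 + rho)/2, which is 0.75 at rho 0.5 and 0.875 at rho 0.75. The change-score analysis then needs 1/0.75 = 1.33 or 1/0.875 = 1.14 times as many participants.

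**Both tests on the same data.** Let the arm differences be a at T2 and b at T3, in SD.
- Planned interaction: lambda = (n/2) × (2/3)(a² + b² − ab)/(1 − rho).
- Baseline-adjusted joint test of T2 and T3: lambda = (n/2) × [(1 + rho)(a² + b²) − 2 rho ab]/[(1 − rho)(1 + 2 rho)].

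For a sustained effect of 0.38 SD, (n/2)a² = 27.5 × 0.1444 = 3.971. At rho 0.5 the interaction has lambda 3.971 × 0.667/0.5 = 5.29 and the joint test 3.971 × 2/(0.5 × 2) = 7.94. At rho 0.75 they are 10.59 and 12.71. An effect of 0.38 SD is a fair calibration: at rho 0.75 the planned test then has power 0.83 at alpha 0.05, close to the stated 0.85.

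Power at N = 110, alpha 0.0083, from noncentral F and simulation (the methods differ by 0.01 to 0.02):

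| effect at T2, T3 (SD) | correlations | planned interaction | adjusted joint test |
|---|---|---|---|
| 0.38, 0.38 | all 0.5 | 0.26 | 0.44 |
| 0.38, 0.38 | all 0.75 | 0.60 | 0.71 |
| 0.38, 0.19 | all 0.5 | 0.18 | 0.27 |
| 0.38, 0.19 | all 0.75 | 0.44 | 0.51 |
| 0.38, 0 | all 0.5 | 0.27 | 0.30 |
| 0.38, 0 | all 0.75 | 0.62 | 0.63 |
| 0.38, 0.38 | T1–T2 0.6, T2–T3 0.85, T1–T3 0.6 | 0.38 | 0.37 |

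The last row has epsilon of about 0.78, near the plan's 0.75, and uses the Greenhouse-Geisser correction for the planned test.

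**Scaled to the plan's effect size.** With equal correlations, eta-squared 0.01 corresponds to a sustained 0.426 SD, since 0.426² = 0.0101 × 110 × 3 × 3/(2 × 27.5). At alpha 0.0083 power goes from 0.35 to 0.56 (rho 0.5) and from 0.74 to 0.83 (rho 0.75).

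**One-degree-of-freedom average of T2 and T3, adjusted for baseline.** At rho 0.75 and 0.38 SD it has power 0.81 if the effect is sustained, but 0.19 if the effect is at T2 only, against about 0.6 for the planned test.

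**The case against.** The planned interaction is a legitimate test in a randomised two-by-three design. A reader might infer that chance baseline imbalance biases it; averaged over randomisations it does not, so only efficiency is at issue. That objection stands and sets the weight of the point.

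A reader might also infer that the plan never says which arm is better, or when. The article does plan contrasts after a significant interaction, although they are conditional and not named. The joint T2/T3 test is equally non-directional and also needs follow-up estimates, so non-directionality is no argument for changing.

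A third tempting reading is that the sphericity provisions are a fault in themselves. The epsilon of 0.75 shows that a correction was foreseen, and such corrections are routine. The sentence "If violations are detected, robust methods, data manipulation, or statistical corrections will be applied accordingly" covers all model assumptions, and a mixed model would not make it redundant.

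The strongest objection concerns size. The gain depends on two unstated quantities, and two plausible cases in the table show essentially none. This also stands, and the gain must be given as a range. On the other side, the joint test was not materially worse in any pattern tried, and the Background section reports benefit lasting to six months in an earlier study, which makes a sustained effect reasonable to plan for.

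Finally, the order of baseline and allocation is not explicit for everyone. The 40 actigraphy patients are described as allocated and then undergoing the psychometric assessments, and that wording leaves their baseline timing open.

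**Conclusion.** The point holds as one of efficiency. The article commits its six primary tests to an interaction that treats baseline as an outcome, and baseline adjustment would usually give more power from the same participants. At 0.38 SD and alpha 0.0083 with equal correlations of 0.5 to 0.75, the joint adjusted test gains about 11 to 18 percentage points for a sustained effect and 7 to 9 if the effect halves by T3. It gains 1 to 3 for an effect at T2 only, and nothing for a sustained effect with correlations 0.6/0.85/0.6. These figures rest on assumed correlations, effect size and time course.

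The figure of 0.81 for the averaged contrast might suggest a much larger gain. It should not be relied on: it requires an effect that lasts, and the article does not commit to that pattern. The mismatch between powering at 0.05 and testing at 0.05/6 is a separate matter; it makes lost precision more costly but is not evidence for this point.

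**What to change.** For each primary outcome, fit a linear mixed model with T2 and T3 as outcomes and arm, visit, arm-by-visit, baseline score and baseline-by-visit as fixed effects, with unstructured covariance and small-sample degrees of freedom. Make the joint two-degree-of-freedom test of the arm differences at T2 and T3 primary, and report the arm difference with its confidence interval at each visit afterwards. Do not make the T2/T3 average the default.

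No extra participants, visits or questionnaires are needed, and the planned R and SPSS both fit this model. The cost goes beyond one sentence: the power statement must be redone for the new test, with rho and the effect pattern stated, and the mediation and moderation analyses, now built on the general linear model, must be restated. Confirm in the text that baseline is completed before allocation for the 40 actigraphy patients too. Make the change before any data by arm are seen.

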### Measures

#### Self-report measures

The Multiple Sclerosis Quality of Life*-*54 questionnaire is a multidimensional health-related quality of life measure that combines both generic and MS-specific items in a single instrument [21]. It is composed of 12 subscales along with two summary scores, and two additional single-item measures. The subscales are: physical function, role limitations, physical, role limitations, emotional, pain, emotional well-being, energy, health perceptions, social function, cognitive function, health distress, overall quality of life, and sexual function. The scale has demonstrated good psychometric properties and has been translated into Italian [22]. This assessment will be completed only by patients.

The Medical Outcomes Study Short*-*Form*-*36 health survey will be used to assess caregivers’ quality of life. This is a 36-item scale constructed to survey health status and quality of life [23], that investigates eight health aspects: limitations in physical activities because of health problems; limitations in social activities because of physical or emotional problems; limitations in usual role activities because of physical health problems; bodily pain; general mental health; limitations in usual role activities because of emotional problems; vitality; general health perceptions. It is one of the most widely used instruments for the evaluation of quality of life in many countries in the world, including Italy [24].

The Hospital Anxiety and Depression Scale will be used to assess depression and anxiety levels of all the subjects. This comprises 14 items rated on a four-point Likert scale [25]. It is designed to screen for the presence and severity of depression and anxiety in patients with a physical symptomatology. The scale mainly includes items that are not related to somatic symptoms of depression.

The Langer Mindfulness Scale will be used to assess the level of meditation attunement. This is a 14-item questionnaire that assesses three domains associated with mindful thinking: novelty seeking, engagement, and novelty producing [26]. An individual who seeks novelty perceives each situation as an opportunity to learn something new. An individual who scores high in engagement is likely to notice more details about his or her specific relationship with the environment.

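### The six primary tests use a fixed 0.008 threshold where Holm's step-down would keep the same 5% error with more power, and the count of six depends on one prespecified quality-of-life score per population

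*Protocol article*

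**What the plan says.** The Analysis section sets out a repeated-measures comparison: "The general linear model will be used to test interaction effects between treatments (experimental versus control groups) and over time (three repeated measures". It then fixes the number of primary tests: "Six models will be built, one of each primary outcome measure (quality of life, anxiety, and depression) and separately for patients and caregivers". The multiplicity rule follows: "Type I error inflation due to multiplicity of tests will be controlled by the correction of critical alpha (0.05/6 = 0.008").

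The section on screening, assessments and randomization names the primary domains without naming a score: "Primary outcome measures will assess quality of life, together with depression and anxiety".

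The Self-report measures section describes the two quality-of-life instruments. Of the MSQOL-54 it says "It is composed of 12 subscales along with two summary scores, and two additional single-item measures", and then "This assessment will be completed only by patients". Caregivers complete the SF-36, a scale "that investigates eight health aspects". Neither description mentions one overall total. One of the 12 MSQOL-54 subscales is itself labelled overall quality of life.

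The sample-size statement in the Analysis section gives its figures "with a 0.85 statistical power, alpha = 0.05 and an assumed nonsphericity correction" of 0.75, for 110 patients (and caregivers). It does not state the correlation between repeated measures.

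**The concern.** There are two linked matters.

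**Efficiency.** A single fixed threshold for all six tests discards power. Once one hypothesis has been rejected, at most five can still be true, so the next smallest p-value can be compared with 0.05/5 without raising the family-wise error, and so on. Holm's procedure does this; the fixed 0.008 rule does not. The loss matters here because the sample size was worked out at 0.05 while the tests are judged at about one sixth of that, so power at the corrected threshold is below the quoted 0.85.

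**The count.** Three outcomes in two populations make six only if quality of life is one variable in each population. The instruments as described offer several candidates, and the article does not select among them. If more than one score were tested as primary at 0.008, or if one were picked after results had been seen, the 5% limit would no longer be assured. Quality of life is the central outcome of the trial, so a primary claim on it should not be open to that question.

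**Working it through.** **1. The plan's own figure.** Models: 3 outcomes × 2 populations = 6. Threshold: 0.05/6 = 0.00833, printed as 0.008. Upper bound on the family-wise error under any dependence: 6 × 0.00833 = 0.050 (6 × 0.008 = 0.048 with the rounded value). If the tests were independent: 1 − (1 − 0.00833)^6 = 0.049, or 1 − 0.992^6 = 0.047. The correction is right for six tests.

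**2. Holm over the same six p-values.** Order the p-values from smallest to largest and compare them in turn with 0.05/6, 0.05/5, 0.05/4, 0.05/3, 0.05/2 and 0.05, that is 0.0083, 0.0100, 0.0125, 0.0167, 0.0250 and 0.0500. Stop at the first that fails. The first step equals the Bonferroni threshold and every later step is more lenient. Anything Bonferroni rejects is therefore also rejected by Holm, and the family-wise error stays at or below 5% whatever the dependence.

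**3. The baseline power is an assumption.** Power for the group-by-time interaction was computed from the noncentral F distribution with 2 groups, 3 times, N = 110, η² = 0.01 (f² = 0.01/0.99), ε = 0.75 and λ = f² × N × 3 × ε/(1 − ρ). The correlation ρ between repeated measures is not in the article.

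| ρ (assumed) | power at 0.05 | power at 0.05/6 |
|---|---|---|
| 0.5 | 0.54 | 0.28 |
| 0.7 | 0.77 | 0.52 |
| 0.75 | 0.84 | 0.62 |
| 0.8 | 0.91 | 0.75 |

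The stated 0.85 at alpha 0.05 is reached at ρ of about 0.755, where power at 0.05/6 is 0.64. A baseline of 0.62 (ρ = 0.75) is therefore close to what the plan's own sample-size statement implies, but it is not a figure the plan gives.

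**4. Gain from Holm.** Six two-sided normal tests were simulated. Each real effect was set to give power of 0.62 at 0.05/6, and the correlation r between tests was 0 or 0.5 (assumed).

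| real effects | Bonferroni, mean per-test power | Holm, r = 0 | Holm, r = 0.5 |
|---|---|---|---|
| 6 of 6 | 0.62 | 0.75 | 0.72 |
| 3 of 6 | 0.62 | 0.65 | 0.65 |
| 1 of 6 | 0.62 | 0.62 | 0.62 |

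The gain grows with the number of real effects and vanishes when only one is real.

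**5. If the family were larger than six.** At 0.008 per test, with independent tests, the chance of at least one false positive is 1 − 0.992^m.

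- m = 7 (both MSQOL-54 summaries, one SF-36 score, four anxiety and depression tests): 1 − 0.992^7 = 5.5%.
- m = 14 (both MSQOL-54 summaries, all eight SF-36 aspects, the same four): 1 − 0.992^14 = 10.6%.

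The upper bounds under any dependence are 7 × 0.008 = 5.6% and 14 × 0.008 = 11.2%. Scores from one questionnaire are correlated, so the true error would probably lie below the independence figures. Both families are illustrations; the article plans neither.

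**The case against.** The strongest reply is that nothing here is an error. Bonferroni is valid, the divisor matches the number of models declared, and choosing a simple rule is the sponsor's right. That stands. The case for Holm is that it is an improvement at no cost in data or sample size, not that the present rule fails. The size of the gain also rests on an assumed baseline power, and the upper figure needs all six effects to be real, which is the case most favourable to Holm.

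A second reply is that a condensed article commonly leaves the choice of score to the full protocol or the statistical analysis plan, neither of which is shown. That largely stands too. It cannot be said that the plan leaves the score unchosen, only that this article does not show the choice. If a fuller document names one score per population, citing it closes this part.

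A reader might go further and infer that 0.05/6 does not match the family it protects, because the instruments yield 12 subscales, two summaries and eight aspects. The article does not support that reading. It commits to six models, and describing an instrument's scores does not make each of them a primary endpoint. Nor does it follow that type I error control necessarily fails: with one score fixed in advance in each population, control is delivered as stated.

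**Conclusion.** The fixed threshold of 0.008 is correct for six tests but less efficient than it need be. Under the assumed baseline of 0.62, Holm raises mean per-test power by about 0.10 to 0.13 if all six effects are real, by about 0.03 if three are, and by practically nothing if only one is. It never does worse, and the 5% family-wise limit is unchanged.

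The count of six is conditional. It holds if one quality-of-life score per population is fixed before outcomes are seen, and the article does not show that this was done. With one extra score the excess would be slight; only with all eight caregiver aspects counted as primary would the error roughly double. This part is a request for confirmation, not a finding that the error rate is wrong.

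**What to change.** In the Analysis section, replace the fixed 0.05/6 threshold with Holm's step-down procedure over the primary p-values at a family-wise level of 0.05, using unrounded thresholds.

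Add one sentence that names the score entering the quality-of-life model for patients and the one for caregivers, or cites the document where they are already named. All other quality-of-life scores then become secondary. If more than one score is to stay primary, for example both MSQOL-54 summaries, include each in the Holm family so that the first step is 0.05 divided by the actual number of tests (0.05/7 = 0.0071 in that example). The article reports that recruitment is ongoing, so the choice should be recorded before any outcome is examined by arm.

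The cost is about two sentences, with no change to data collection or sample size. The downside is that scores not chosen cannot carry a primary claim.

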### Sample size and recruitment

We aim to recruit 120 people with MS together with their primary caregivers (therefore, the potential sample is up to 240 subjects; 120 patients and 120 caregivers).

Inclusion criteria for patients with MS will be:Diagnosis of relapsing-remitting or secondary progressive MS (divided into 60 relapsing-remitting and 60 secondary progressive during the recruitment procedure);Ability to communicate and to understand tasks;No change of disease-modifying treatment in the 3 months before the enrolment;No clinical relapses or use of steroid treatment during the 4 weeks before the enrolment;Availability of a personal computer, smartphone, or tablet (compatible with the software);Provided informed consent for study participation;Age >18 years.

Inclusion criteria for caregivers will be:Being a person who lives with the MS patient and provides him or her with the most care and assistance;Ability to communicate and to understand tasks;Availability of a personal computer, smartphone, or tablet (compatible with the software);Provided informed consent for study participation;Age >18 years.

Exclusion criteria (referred to both patients and caregivers) will be:Severe co-morbidity that would reduce life expectancy to less than one year (e.g., end-stage oncological diseases or severe cardiac dysfunction);Severe neuropsychological impairment (e.g., dementia), as indicated by testing below the fifth percentile in at least 3 of 6 dimensions of neuropsychological functioning tests (i.e., attention and concentration, processing speed, executive function, verbal memory, and verbal processing);Psychosis or dissociative disorders;Pregnancy.

Subjects will be recruited at the Multiple Sclerosis Center of the Fondazione Don Gnocchi Hospital, in Milan.

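### The six primary interactions are tested at a fixed Bonferroni threshold; Holm's step-down procedure holds the same familywise error and recovers part of the lost power when several effects are real

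*Protocol article*

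**What the plan says.** All of this stands in the Analysis section of the protocol article.

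- The test: "The general linear model will be used to test interaction effects between treatments (experimental versus control groups) and over time (three repeated measures").
- The family: "Six models will be built, one of each primary outcome measure (quality of life, anxiety, and depression) and separately for patients and caregivers".
- The decision rule: "Type I error inflation due to multiplicity of tests will be controlled by the correction of critical alpha (0.05/6 = 0.008"). One threshold serves all six tests. The section describes no ordering of hypotheses, step-down rule or gatekeeping.
- The power statement: "a total sample size of 110 patients (and caregivers") is said to detect "small interaction effects (*η*^2^ = 0.01) with a 0.85 statistical power", with "alpha = 0.05 and an assumed nonsphericity correction (*ε*) of 0.75". The 0.05 here is the uncorrected level.
- Contrasts follow only where an interaction is significant. No simultaneous confidence intervals are planned for the six tests.

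**The concern.** A fixed threshold of 0.05/6 holds the sixth-smallest p-value to the same standard as the smallest. Once some hypotheses have been rejected, familywise control no longer requires this. Holm relaxes the threshold after each rejection and keeps the same error guarantee, so the fixed rule can only lose rejections.

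At stake is the chance of showing benefit on more than one outcome or in both populations. The Discussion states the aim for people with MS and their caregivers alike, so the trial hopes for several positive results. Several real effects is also the setting in which the choice between the two rules matters most.

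**Working it through.** **1. The plan's own figure.** 0.05/6 = 0.00833, printed as 0.008. If the six tests were independent, familywise error would be 1 − (1 − 0.00833)^6 = 0.0490, or 1 − (1 − 0.008)^6 = 0.0471 with the rounded value. The figure reproduces and the control is valid.

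**2. Holm on the same family.** Order the p-values p(1) ≤ … ≤ p(6). Compare p(j) with 0.05/(7 − j), that is 0.0083, 0.0100, 0.0125, 0.0167, 0.0250, 0.0500, and stop at the first non-rejection.
- *Error control.* Suppose m0 of the six nulls are true. When the first true null is rejected, at most 6 − m0 hypotheses have been rejected before it, so its p-value is at most 0.05/m0. By the union bound, the chance that any of the m0 true nulls has so small a p-value is at most m0 × 0.05/m0 = 0.05, whatever the dependence.
- *Dominance.* Every Holm threshold is at least 0.05/6, so whatever Bonferroni rejects, Holm rejects.
- *First rejection.* Both rules reject something exactly when p(1) ≤ 0.05/6.

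**3. What Bonferroni costs per test.** Treat each interaction as a 2-df chi-square test. Power of 0.85 at 0.05 requires noncentrality 10.92, and the same noncentrality gives 0.644 at 0.05/6. The loss is 0.85 − 0.644 = 0.206.

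As a check, use the noncentral F with df1 = 2 × 0.75 = 1.5, df2 = 108 × 2 × 0.75 = 162, f² = 0.01/0.99 and λ = f² × 110 × 3 × 0.75/(1 − ρ) = 2.5/(1 − ρ). The article does not give ρ, the correlation between repeated measures. Power at 0.05 is 0.54 for ρ = 0.5, 0.84 for ρ = 0.75 and 0.85 for ρ = 0.755. At ρ = 0.755, power at 0.05/6 is 0.637, close to the 0.644 above.

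**4. What Holm returns.** Simulation of six 2-df tests, 200,000 runs per setting. The correlation r between tests and the number of real effects are assumptions. Entries are average power per true effect, Bonferroni → Holm.

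| Power at 0.05 | Real effects | r = 0 | r = 0.5 |
|---|---|---|---|
| 0.85 | 6 | 0.6440 → 0.7687 | 0.6444 → 0.7471 |
| 0.85 | 3 | 0.6433 → 0.6764 | 0.6447 → 0.6734 |
| 0.85 | 1 | 0.6443 → 0.6452 | 0.6443 → 0.6449 |
| 0.54 | 6 | 0.2850 → 0.3285 | 0.2835 → 0.3452 |
| 0.54 | 3 | 0.2843 → 0.2979 | 0.2835 → 0.3009 |
| 0.54 | 1 | 0.2837 → 0.2847 | 0.2852 → 0.2859 |

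A second run at 0.85, with r = 0.5 within a population and 0.2 across, gave 0.643 → 0.753 (six effects), 0.645 → 0.674 (three) and 0.644 → 0.658 (two). With two effects and r = 0 it gave 0.644 → 0.659.

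- *Share of the loss recovered, six effects, power 0.85:* 0.1247/0.206 = 61% at r = 0; 0.1027/0.206 = 50% at r = 0.5. *Three effects:* 0.0331/0.206 = 16% and 0.0287/0.206 = 14%.
- *Power to show all six, power 0.85:* 0.071 → 0.337 (r = 0) and 0.261 → 0.529 (r = 0.5).
- *At least one true effect found, power 0.85:* 0.9979 under both rules with six effects at r = 0; 0.8674 against 0.8677 with three effects at r = 0.5.
- *Familywise error under Holm:* at most 0.049 in every setting.

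**The case against.** **Nothing in the plan is wrong.** Bonferroni is valid under any dependence, its arithmetic is right, and it is prespecified. This stands. A reader might infer that type I error is badly controlled; the Analysis section does not support that. The point is only that a rule at least as powerful in every case exists at the same error rate. Nor is it a detail that the article leaves to an unseen analysis plan, because the article fixes the threshold itself.

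**The gain may be small.** This stands too. The largest figures need all six effects to be real, and the article does not claim that: the Background says caregiver benefit has not been explored in depth, and the Discussion treats it as a question for the trial. If only the three patient outcomes respond, the gain is about 3 points, or 1–2 if power at 0.05 is 0.54. It would be too strong to say that Holm returns the power lost or rescues the sample size. Recovery is partial, and the first rejection still needs p ≤ 0.0083.

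**Correlated outcomes.** A reader might infer that outcomes moving together make this the setting where Bonferroni wastes most. The article states no correlations, Holm makes no use of them, and the simulations show no such pattern. With six effects and 0.85 power, the gain is smaller with correlation (10.3 against 12.5 points). At 0.54 power it is larger (6.2 against 4.4).

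**Confidence intervals.** Simultaneous intervals that match Holm are less simple than Bonferroni intervals. This is true in general but has little force here: the primary tests are omnibus interactions and no such intervals are planned.

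**Conclusion.** The point holds as a low-cost efficiency improvement. For the six tests as specified, Holm never rejects fewer hypotheses than the fixed threshold and has the same familywise guarantee; that part is proved and needs no assumption. The size of the gain does rest on assumptions: the 2-df approximation, the true power at 0.05, the correlation between tests and the number of real effects. On the stated 0.85, the gain in average power per true effect is about 10–12 points with six real effects, 3 with three, 1.5 with two and practically none with one. On 0.54, it is 4–6 points with six and 1–2 with three.

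The mismatch between a power calculation at 0.05 and testing at 0.008 is a separate and larger matter. At ρ = 0.755, power of 0.85 at 0.05/6 needs about 164 per population, against the 110 in the power statement and the recruitment target ("We aim to recruit 120 people with MS together with their primary caregivers"). Holm does not close that gap.

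**What to change.** In the Analysis section, replace the fixed 0.008 with Holm's procedure over the same six interaction tests: smallest p-value against 0.05/6 = 0.00833 (unrounded), next against 0.05/5, and so on up to 0.05, stopping at the first non-rejection. Report Holm-adjusted p-values, where the adjusted p(j) is the largest of min(1, (7 − i) × p(i)) over i ≤ j. Let the follow-up contrasts depend on an adjusted value of at most 0.05.

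The cost is one sentence, documented before any unblinded analysis. No further participants, visits or data are needed; the procedure uses only the six p-values already planned. If simultaneous confidence intervals are added later, they will be less simple than under Bonferroni. The sample-size statement should be reconciled with the testing level separately.
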